## Methods/Design

### Study Aims and Hypotheses

The overall study aim is to compare the efficacy of peer-delivered telephone support with DVD educational resource, vs. oncology nurse-delivered telephone counselling with DVD educational resource, vs. usual care in improving both men's and women's sexual and psychosocial adjustment at 3, 6 and 12 months after treatment for localised prostate cancer. In doing so we will also compare the cost-effectiveness of support by trained peers vs. nurse counsellors; and identify demographic, medical and psychosocial variables that predict improvement in psychosexual adjustment in prostate cancer patients and their partners with each intervention approach.

The intervention will utilise a cognitive behavioural approach that has been found to be effective in promoting positive adjustment after cancer [30], along with couple relationship education focussed on relationship enhancement and helping the couple to conjointly manage the stresses of cancer diagnosis and treatment [19]. The study will have three arms: (1) usual care (2) telephone support by a trained male peer support volunteer who is a prostate cancer survivor with DVD education and (3) oncology nurse-delivered telephone counselling with DVD education.

It is hypothesised that 3, 6, and 12 months after surgery for localised prostate cancer:

1. By contrast to couples in usual care, couples who receive either the peer or nurse delivered intervention will have a more positive sexual adjustment; lower unmet sexuality supportive care needs; more positive attitudes to sexual help seeking; higher uptake of erectile aids; improved psychological adjustment and quality of life.

2. Couples who receive the peer and nurse delivered intervention will have similar sexual adjustment; sexuality supportive care needs; attitudes to sexual help seeking; uptake of erectile aids; psychological adjustment and quality of life.

3. The peer delivered intervention will be more cost effective by comparison to the nurse delivered intervention.

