A cost-utility analysis will also be undertaken to address Hypothesis 3 where intervention resources and health outcomes are combined in an analysis to produce information on the relative economic efficiency between the peer, nurse specialist and usual care options. The analysis will take the perspectives of the health provider and health system and involve the assessment of 1) cost data on resources used in each of the three arms by identifying, quantifying and valuing resources using standard methods and, 2) health outcomes, in terms of quality-adjusted life years (QALYs). Using Medicare Australia data, we also wish to capture health utilisation costs for GP visits and medication use to assess whether the interventions change typical health care use. Quality of life will be measured in participants using the preference-based utility instrument SF-6D [49] which is based on the SF-36 quality of life tool. The key outcome for the cost-utility analysis will be the *incremental cost-effectiveness ratio*, expressed as the incremental cost per QALY. This ratio represents the difference in costs between the intervention and usual care options divided by the difference in QALYs gained across the two options. This means that it is the *additional *cost and health benefits of each of the two interventions over and above what occurs in usual care that is important. Secondary economic endpoints will include incremental cost-effectiveness ratios for cost per % gain in sexual function and psychological distress. A Bayesian statistical approach to the analysis will be followed so that probabilistic statements on the efficiency of the intervention will be produced [50]. Data will be analysed using the computer program TreeAge Pro (Healthcare Module) 2005 [51]. The results will be scrutinised using probabilistic sensitivity analysis which is standard practice in economic evaluations to address data uncertainty and potentially strengthens the generalisability of the results. Specifically, Monte Carlo simulations will produce cost-effectiveness acceptability curves and probabilistic statements on cost-effectiveness.

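### Hypothesis 3 compares peer with nurse delivery, but the key economic outcome is each intervention's ratio against usual care, which does not estimate that contrast and can rank the two wrongly

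*Protocol article*

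**What the plan says.** In the protocol article, Study Aims and Hypotheses, Hypothesis 3 is a head-to-head statement: "The peer delivered intervention will be more cost effective by comparison to the nurse delivered intervention". The study aim in the same section matches it: "In doing so we will also compare the cost-effectiveness of support by trained peers vs. nurse counsellors".

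The Statistical Analyses section links the method to that hypothesis: "A cost-utility analysis will also be undertaken to address Hypothesis 3". It gives the purpose as "to produce information on the relative economic efficiency between the peer, nurse specialist and usual care options". The key outcome is the ICER, "expressed as the incremental cost per QALY", and its comparator is fixed: the "difference in costs between the intervention and usual care options divided by the difference in QALYs gained across the two options". The next sentence interprets this: it is the additional "cost and health benefits of each of the two interventions over and above what occurs in usual care that is important".

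For uncertainty, "Monte Carlo simulations will produce cost-effectiveness acceptability curves and probabilistic statements on cost-effectiveness". The text does not say which options those curves compare. The same section names contrasts on study condition for Hypotheses 1 and 2 only.

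**The concern.** The hypothesis asks whether peer or nurse delivery is the better use of resources. The outcome assigned to it asks, twice over, whether an intervention is worth adding to usual care. These are different questions.

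With mutually exclusive options, two ratios against a common comparator do not show which option to choose. That depends on what the dearer option adds over the cheaper one, or equivalently on which has the higher net benefit at the payer's threshold. A cheap option with a small gain can have the lower ratio and still be the less efficient choice.

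At stake is the conclusion on one of the trial's three hypotheses, and with it the recommendation on efficient service delivery promised in the abstract. The article does not merely leave a detail to an analysis plan: it states a comparator, and the comparator does not match the hypothesis.

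**Working it through.** **The plan's own figures.** The article gives no cost, QALY or threshold value, so there is no economic figure to reproduce. Its one design figure, power of 0.8 for d = 0.5 at alpha .05 with 70 couples per condition and 10% attrition (Participants), does reproduce: 70 × 0.9 = 63 per arm gives 0.801 (two-sided, normal approximation). It plays no part in this point.

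**Formulas.** Let C and Q be an option's cost and QALY increments over usual care, and λ the willingness to pay per QALY.
- Stated outcome: R = C / Q, one for peer (Rp) and one for nurse (Rn).
- Contrast that Hypothesis 3 needs: (Cn − Cp) / (Qn − Qp), or the difference in net monetary benefit, where NMB = λQ − C.
- Link between them: (Cn − Cp) / (Qn − Qp) = Rn + Qp(Rn − Rp) / (Qn − Qp).

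If both gains are positive, nurse gains more and peer has the lower stated ratio, the direct ratio lies above both stated ratios. Nurse is then the better choice at every λ above the direct ratio, although the stated ratios favour peer.

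**Illustration (all values assumed, in currency units).** Peer: C = 200, Q = 0.010, so Rp = 200/0.010 = 20,000. Nurse: C = 500, with Q varied.

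| Nurse QALY gain | Nurse vs usual care | Lower stated ratio | Nurse vs peer | Higher net benefit |
|---|---|---|---|---|
| 0.010 | 500/0.010 = 50,000 | peer | 300 more for no gain | peer at every λ |
| 0.012 | 500/0.012 = 41,667 | peer | 300/0.002 = 150,000 | peer below 150,000, nurse above |
| 0.020 | 500/0.020 = 25,000 | peer | 300/0.010 = 30,000 | peer below 30,000, nurse above |
| 0.030 | 500/0.030 = 16,667 | nurse | 300/0.020 = 15,000 | peer below 15,000, nurse above |

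For the third row:
- λ = 20,000: NMB is 200 − 200 = 0 for peer and 400 − 500 = −100 for nurse.
- λ = 30,000: 300 − 200 = 100 and 600 − 500 = 100, the switch point.
- λ = 50,000: 500 − 200 = 300 and 1,000 − 500 = 500.

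The stated ratios (20,000 and 25,000) are the same throughout and do not show the switch at 30,000.

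**Negative gains.** If peer had C = 200 and Q = −0.005, its ratio would be 200/(−0.005) = −40,000. This cannot be ranked against a positive ratio, whereas NMB remains defined (at λ = 20,000, −100 − 200 = −300).

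**The case against.** **The scope sentence and the simulations cover three options.** This stands. The opening sentence on the cost-utility analysis names peer, nurse and usual care, costs are collected in each arm, and acceptability curves run over willingness to pay, which is a net-benefit framework. Nothing says that they are restricted to comparisons with usual care, so the planned data and simulations could give the direct contrast. The defect is in how the key outcome is defined and interpreted. The scope sentence does not repair it, because the later and more specific sentences fix the comparator.

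**The sentence on what is important may only explain the word incremental.** That is a fair reading, and it does not expressly exclude a peer-versus-nurse contrast. The contrast can also be had by subtraction, but only from the separate cost and QALY increments; the two ratios alone do not give it.

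**Hypothesis 2 expects similar quality of life, so cost would decide.** With equal positive gains this is right, as the first row of the table shows. But similarity is itself under test, and estimated gains will not be exactly equal.

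**A nurse-versus-peer ratio would be unstable too.** This is correct: under Hypothesis 2 its denominator is the one expected to be nearest zero. It is the reason to prefer incremental net benefit to a second ratio as the main measure.

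**Stronger readings.** A reader might infer that the trial will declare peer delivery the winner whenever its ratio against usual care is lower. The article states no such rule. A reader might also infer that a wrong ranking is likely because volunteers cost little. The Background does call peer support inexpensive, but says that the saving is not yet quantified, and the article gives no QALY gains or threshold from which to judge.

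**Conclusion.** The point holds as a mismatch between a named hypothesis and its stated key outcome. Hypothesis 3 is peer versus nurse; the defined ICER is each intervention versus usual care, and that pair of ratios does not estimate the hypothesised contrast.

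The consequence is a possible wrong ranking. It arises when the QALY gains differ, the option with the smaller gain has the lower ratio against usual care, and the threshold lies above the direct ratio between the two (30,000 in the third row of the illustration). It does not arise when the gains are equal and positive. The numerical size rests entirely on assumed costs and gains, so no probability can be attached to it.

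The definition should be corrected before analysis. Hypotheses 1 and 2, the primary outcomes, the sample size and the data collection are unaffected.

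**What to change.** In the Statistical Analyses section, define the key outcome for Hypothesis 3 as the peer-versus-nurse incremental cost, incremental QALYs and incremental net monetary benefit across a range of willingness-to-pay values. Place it within a three-option incremental analysis: order the options by cost, remove dominated ones, and report the increment between those that remain. Build the planned acceptability curves on all three options jointly, and report from the same simulations the probability that peer has higher net benefit than nurse at each value. Keep the two ratios against usual care as additional results, since whether each intervention is worth adding to usual care is a useful question in its own right.

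The cost is a change of wording and a few more outputs from data and simulations already planned. No new data, arms or participants are needed.

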## Discussion

This study will address a critical but as yet unanswered research question: to identify a cost-effective and population based approach to promoting optimal psychosexual adjustment for men with prostate cancer and their partners. To date, for this patient group, no sexuality intervention studies have: targeted couples at diagnosis when distress is highest; been adequately powered to look differentially at intervention effects; trialled peer support; or included economic analyses. This research will overcome these limitations. The intervention will be able to be utilised by trained nurses in a range of settings including broad reach tele-health lines and also through peer support programs that are conducted internationally. This means that project outputs will be immediately translatable into practice to improve the sexual health and overall well-being of men with prostate cancer and their partners.
